### Randomization

Before enrolling the first study participant, a research statistician generated the balanced randomization scheme for treatment allocation at both clinical sites using the R Statistical Package.^21^ This method randomly assigns participants to one of three intervention groups (*N* = 20 per group): 1) tAIH + WALK_tSTIM_, 2) tAIH + WALK_tSHAM_, and 3) Placebo + WALK_tSTIM_ in blocks of 6 participants. Using this scheme, the site coordinator will assign each participant to their respective intervention group in the order in which they complete the walking practice sessions. Although the coordinator informs participants about their possible group assignment, they will be blinded to the treatment they receive (i.e., tAIH or Placebo, WALK_tSTIM_, or WALK_tSHAM_). The clinical raters and trainers will also be unaware of each participant's treatment assignment. Based upon reports from participants blinded during our previous tAIH study,^6^ >75% guessed incorrectly or were uncertain of the breathing intervention received, suggesting that our previous blinding and air delivery methods were effective.

We plan a similar integrity analysis for the stimulation sham protocols (no stimulation). Participants guess the interventions received at the end of each treatment session and indicate their guess confidence using a Likert scale.^22,23^ Using a contingency table and Fisher's exact test, we will determine whether the probability of correct guessing differs from chance.

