### Sample size

We plan to enroll *N* = 60 persons with chronic, incomplete SCI in this clinical trial. We created a Consolidated Standard of Reporting Trials (CONSORT) flow diagram (Fig. 2) to summarize our trial enrollment, intervention, allocation, follow-up, and analyses.^19^ The initial sample size is an estimate from conservative power calculations on preliminary data that support our hypotheses testing in Aims 1 and 2.

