### Study recruitment and enrollment

We established an interprofessional recruitment team at Spaulding Rehabilitation Hospital and Shirley Ryan AbilityLab. The recruitment team comprises the site principal investigators, clinical trial coordinators, research assistants, post-doctoral research fellows, onsite physicians, and research physical therapists. Our study recruitment process includes reviews of site-specific hospital patient registries, announcements through clinical research networks (e.g., Spinal Cord Injury Model Systems), clinicaltrials.gov, outreach to local outpatient rehabilitation centers, and media postings on relevant websites. Our team clinicians will also contact patients with SCI diagnoses admitted to our clinical sites that will likely meet the study criteria once they reach the chronic stage of injury. The study personnel contact potential participants using IRB-approved scripts to avoid bias or coercion during recruitment. Study participants must meet the study inclusion and exclusion criteria detailed in Table 1. These criteria align with the International Campaign for Cures of Spinal Cord Injury Paralysis recommendations^24^ and account for ethical considerations, safety, and potential confounds during participant recruitment.

**Table 1. tb1:** Study Eligibility Criteria

Inclusion criteria
• 18–70 years of age
• Medically stable with medical clearance from study physician to participate
• Incomplete SCI at and between levels C_2_ and L_2_ with at least some sensory or motor function preserved below the neurological level to ensure phrenic and cauda equina sparing
• Non-progressive etiology of SCI
• ISNCSCI Impairment Scale,^69^ Grade C–D
• Ambulatory, able to walk 10 meters without support from another person
• Chronic injury (≥12 months post-injury)^a^
Exclusion criteria
• Severe concurrent illness or pain^b^
• Less than a score of 24 on the MMSE^c^
• Severe recurrent autonomic dysreflexia per assessment by the study physicians
• History of severe cardiovascular/pulmonary complications, including hypertension (systolic blood pressure >150 mm Hg)
• Pregnancy^d^
• Botulinum toxin injections in lower extremity muscles within the last 6 months
• History of tendon or nerve transfer surgery in the lower extremity
• Untreated severe sleep-disordered breathing^e^
• Active implanted devices (e.g., intrathecal baclofen pump)
• Receiving electrical stimulation therapy

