To minimize biases and errors in data collection, a designated lead physical therapist, blinded to study interventions, ensures participant adherence to the protocol and consistent scoring among therapists by regularly checking all assessment logs for adherence to standard clinical procedures. Non-blinded research staff members (including post-doctoral fellows, lab engineers, and research assistants) assist clinicians with training setup and clinical data collection. The study principal investigator oversees all study procedures and ensures the correct collection and documentation of data. If participants miss more than two walking practice sessions or intervention sessions, we will not conduct further assessments and exclude their data from analyses. However, if participants miss an assessment session, we record their data as “missing” at that time point.

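### A site coordinator whose role also recruits assigns from a scheme with one disclosed block size of 6, after a two-week run-in, so some upcoming assignments can be predicted if earlier ones are known at the site

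*Protocol article*

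**What the plan says.** The Randomization section of the Protocol article states that, before the first enrolment, "a research statistician generated the balanced randomization scheme for treatment allocation at both clinical sites". Allocation is to three arms of 20, "in blocks of 6 participants". With this scheme, "the site coordinator will assign each participant to their respective intervention group in the order in which they complete the walking practice sessions". Participants, raters and trainers are to be blinded.

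Other sections describe the people and the timing:

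- **Recruiters** (Study recruitment and enrollment): "The recruitment team comprises the site principal investigators, clinical trial coordinators, research assistants, post-doctoral research fellows", together with physicians and research physical therapists.
- **Non-blinded staff** (closing paragraph of Statistical analysis): post-doctoral fellows, laboratory engineers and research assistants, who help with training set-up and data collection. The section on spinal stimulation adds the team member who configures the stimulator.
- **Run-in** (Walking practice; Fig. 3 legend): eight practice sessions over two weeks, with the T0 assessment at the end of week 2.
- **Exit before allocation** (Statistical analysis): "If participants miss more than two walking practice sessions or intervention sessions, we will not conduct further assessments", and the data are excluded.

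**The concern.** Randomisation prevents selection bias only if nobody who can affect which participant is assigned next can foresee the next assignment. Here the article names a local role, one that also recruits, as the user of a pre-generated scheme. It discloses a single block size, and it lists two further roles that both recruit and are non-blinded. Assignment comes late, when the site has already seen two weeks of walking on the tasks that form the primary outcomes.

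If the next slot can be foreseen, and if it is open who fills it, participants in the three arms could differ in ways that the site has observed but the data do not record, such as motivation, fatigue or perceived responsiveness. Adjusting for a walking score removes only the part that the score captures. With 20 per arm in a population that Study limitations itself calls heterogeneous, a few such assignments could matter. Blinded rating protects against biased assessment, not against this.

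**Working it through.** **The plan's own figures.** The article gives no figure for predictability. Its allocation numbers are consistent: 16 completers / (1 − 0.20) = 20 per arm; 3 × 20 = 60; 60 / 6 = 10 blocks. A balanced scheme with equal arms means two slots per arm in each block of 6.

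**Model.** An observer knows the block size and every earlier three-arm assignment in the current block. There are 6! / (2!·2!·2!) = 90 equally likely orders.

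| Slot | Certain in advance | At least one arm ruled out | Best guess correct |
|---|---|---|---|
| 1 | 0 | 0 | 1/3 = 0.333 |
| 2 | 0 | 0 | 2/5 = 0.400 |
| 3 | 0 | 0.2 | 2/4 = 0.500 |
| 4 | 0 | 0.6 | 0.4 × 1/3 + 0.6 × 2/3 = 0.533 |
| 5 | 0.2 | 1 | 0.2 × 1 + 0.8 × 1/2 = 0.600 |
| 6 | 1 | 1 | 1.000 |
| Sum | 1.2 | 2.8 | 3.367 |
| Divided by 6 | 20% | 46.7% | 56.1% |

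The entries arise as follows:

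- Slot 5 is certain when the last two slots belong to the same arm: 3 × 6 / 90 = 0.2.
- An arm is used up before slot 3 when the first two assignments match: 1/5 = 0.2.
- An arm is used up before slot 4 unless the first three assignments all differ: 1 − (4/5 × 2/4) = 0.6.
- After four assignments at least one arm must be used up.

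Over 10 complete blocks, 1.2 × 10 = 12 of 60 assignments are certain, and the best guess is right for 3.367 × 10 = 33.7 of 60, against 20 of 60 by chance.

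**If only stimulation versus sham is known.** Sham takes two of the six slots. That component is certain with probability 1/15, 0.2, 7/15 and 1 at slots 3 to 6, a sum of 1.73 of 6 (29%, about 17 of 60). The full arm is identified only when all remaining slots are sham: 1/15 (slot 5) + 1/3 (slot 6) = 0.4 of 6, or 6.7% (4 of 60). By symmetry the same holds for someone who knows only hypoxia versus placebo air.

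**Effect of varying the block size.** This was simulated over 300 trials of 60, with an observer who knows the possible sizes and updates on each assignment.

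| Block sizes | Certain | Best guess correct |
|---|---|---|
| 6 only | 12.1 of 60 (20%) | 56% |
| 3, 6 | 5.0 of 60 (8%) | 57% |
| 6, 9 | 3.0 of 60 (5%) | 54% |
| 3, 6, 9 | 2.2 of 60 (4%) | 55% |

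Varying the size removes most of the certainty but hardly changes the best guess.

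**The case against.** The strongest reply is that the article says who assigns but not how each assignment is released. Opening the next slot one at a time fits the same words, and a condensed article may leave that detail to the full protocol. This stands. A reader might infer that the coordinator knows every assignment in advance, but the text does not say that the coordinator holds the list or sees future slots. The silence on release is not itself the point. The point rests on what is stated: one block size, a local assigner from the recruiting team, and non-blinded recruiters.

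A reader might also infer that staff can reorder participants, or steer good responders to the combined arm. The documents do not show this. The schedule is fixed, assignment by order of completion limits discretion, and the missed-session rule is a count. Influence on the next slot would need participants whose run-ins overlap at one site, or drop-out before allocation. The second is possible under the stated rule; the frequency of either is not given. Nothing shows that good responders to practice would gain more later, so a direction of bias cannot be asserted.

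Three further replies reduce the concern without removing it:

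- Screening and consent precede the run-in, so selection at consent is narrowed. Selection of who completes, and in what order, is not.
- Hypothesis 1 analyses change from the post-practice assessment, uses analysis of covariance if the groups differ significantly there, and plans a model adjusting for baseline outcomes and demographics. This covers measured differences only.
- The article does not say whether blocks run within site, or which component each non-blinded person knows. Either could weaken prediction.

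**Conclusion.** The point holds in a conditional form. The stated design makes upcoming assignments partly predictable to people who also recruit: 20% certain (about 12 of 60) and a best guess right 56% of the time against 33%. These figures assume two slots per arm in each block, blocks that run within site, earlier three-arm assignments known at that site, and 60 participants allocated in complete blocks.

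Knowledge of one component alone reduces full-arm certainty to about 7%. One list shared across sites, with each site seeing only its own assignments, would also weaken prediction, by an amount that the article does not allow to be calculated. Prediction is complete only for someone who can see the list, and whether the coordinator can is not settled.

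The finding concerns exposure to selection bias. It is not evidence that bias has occurred, and neither its size nor its direction can be computed. The article's sample-size calculation is unaffected. The change is worth making because it is cheap.

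**What to change.** For all remaining participants:

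1. **Controlled release (the main remedy).** The research statistician holds the list. Each assignment is released singly, by site, only after eligibility to continue and the T0 assessment have been recorded and locked. It goes only to the unblinded operators of the air delivery system and the stimulator, not to the coordinator.
2. **Varied blocks.** Use randomly varied block sizes in multiples of 3, not disclosed to the sites. A mix of 3, 6 and 9 cuts certain assignments to about 4% but leaves the best guess near 55%, so this supplements step 1 and does not replace it. A mix of 3 and 6 alone does less.
3. **Text.** State in Randomization who holds the list, when an assignment is released and to whom, and whether blocks run within site. If such a release step already exists, correcting that sentence is most of the work.

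The cost is a regenerated list and a release step, with no extra participants. The drawback is slightly larger possible imbalance: an unfinished block of 9 can leave one arm 3 ahead of another, against 2 with a block of 6, or 6 against 4 if both sites end in mid-block.

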### Study recruitment and enrollment

We established an interprofessional recruitment team at Spaulding Rehabilitation Hospital and Shirley Ryan AbilityLab. The recruitment team comprises the site principal investigators, clinical trial coordinators, research assistants, post-doctoral research fellows, onsite physicians, and research physical therapists. Our study recruitment process includes reviews of site-specific hospital patient registries, announcements through clinical research networks (e.g., Spinal Cord Injury Model Systems), clinicaltrials.gov, outreach to local outpatient rehabilitation centers, and media postings on relevant websites. Our team clinicians will also contact patients with SCI diagnoses admitted to our clinical sites that will likely meet the study criteria once they reach the chronic stage of injury. The study personnel contact potential participants using IRB-approved scripts to avoid bias or coercion during recruitment. Study participants must meet the study inclusion and exclusion criteria detailed in Table 1. These criteria align with the International Campaign for Cures of Spinal Cord Injury Paralysis recommendations^24^ and account for ethical considerations, safety, and potential confounds during participant recruitment.

**Table 1. tb1:** Study Eligibility Criteria

Inclusion criteria
• 18–70 years of age
• Medically stable with medical clearance from study physician to participate
• Incomplete SCI at and between levels C_2_ and L_2_ with at least some sensory or motor function preserved below the neurological level to ensure phrenic and cauda equina sparing
• Non-progressive etiology of SCI
• ISNCSCI Impairment Scale,^69^ Grade C–D
• Ambulatory, able to walk 10 meters without support from another person
• Chronic injury (≥12 months post-injury)^a^
Exclusion criteria
• Severe concurrent illness or pain^b^
• Less than a score of 24 on the MMSE^c^
• Severe recurrent autonomic dysreflexia per assessment by the study physicians
• History of severe cardiovascular/pulmonary complications, including hypertension (systolic blood pressure >150 mm Hg)
• Pregnancy^d^
• Botulinum toxin injections in lower extremity muscles within the last 6 months
• History of tendon or nerve transfer surgery in the lower extremity
• Untreated severe sleep-disordered breathing^e^
• Active implanted devices (e.g., intrathecal baclofen pump)
• Receiving electrical stimulation therapy
• tSTIM-induced involuntary motor threshold is >200 mA (exceeding SCONE's current limit).

^a^
Chronic SCI to avoid the potential for spontaneous neurological plasticity and recovery.^16,70^

^b^
Illness including unhealed decubiti, severe neuropathic or chronic pain syndrome, severe infection (e.g., urinary tract), hypertension, cardiovascular disease, pulmonary disease, severe osteoporosis, active heterotopic ossification in the lower extremities, and severe systemic inflammation.

^c^
MMSE^25^ cutoff to avoid participants with cognitive impairment.

^d^
Pregnancy is an exclusion criterion because of unknown effects of tAIH or tSTIM on a fetus; persons of childbearing potential will not otherwise be excluded.

^e^
Severe sleep-disordered breathing (>30 apneas or hypopneas per hour).^26^

ISNCSCI, International Standards for Neurological Classification of Spinal Cord Injury; MMSE, Mini-Mental State Examination; SCI, spinal cord injury; tAIH, therapeutic intermittent hypoxia; tSTIM, transcutaneous spinal stimulation;

Potential participants undergo a medical screen by the study physicians and a physical/mental evaluation by the clinical research team. Eligible persons are informed of the study procedures and potential risks and sign the IRB-approved informed consent form before participation. The screening consists of a medical record review, assessment of the participant's ability to walk 10 m without human assistance, confirmation that their lower extremity involuntary motor threshold is <200 mA, and Mini-Mental State Examination (MMSE) score ≥24.^25^ We also screen for sleep-disordered breathing using a portable sleep monitor (Nox A1s PSG System; Nox Medical, Suwanee, GA or ApneaLink; ResMed Inc., San Diego, CA) at home for 1 night.^26^ After the screening, we deidentify study participants with a unique alpha-numeric identifier and associate this code with study-related documentation. This study received approval from the MGB IRB (#2022P002036) and the Department of Defense Office of Human Research Oversight in January 2023, and the first study participant enrolled in March 2023.

### Experiment protocol

We developed a study protocol to measure the extent to which tAIH priming boosts the efficacy and potency of training-related functional gains in persons with chronic SCI (Fig. 1). Study participants enroll in 23 intervention and assessment sessions at one of the two clinical trial sites (Fig. 3). Physical therapists serve as trainers and raters; they complete competency and protocol training before their study involvement to ensure rater and training reliability within and between the clinical sites. The interventions consist of eight sessions of walking practice followed by eight combinatorial treatment sessions (four sessions per week for 4 consecutive weeks).

**FIG. 3. f3:**
[figure not shown]
Timeline of interventions and assessments. After the initial screening visit (S), each intervention consists of eight sessions of walking training (WALK) alone, followed by eight additional sessions of tAIH or Placebo before WALK_tSTIM_ or WALK_tSHAM_. Assessments occur at baseline (BL), at the end of intervention weeks 2 (T_0_), 3 (T_1_), and 4 (T_2_), and, again, after 1 (F_1_), 4 (F_4_), and 8 weeks (F_8_) after the last intervention session. tAIH, therapeutic intermittent hypoxia; WALK_tSTIM_, transcutaneous spinal stimulation-enhanced walking therapy.

We anticipate that tAIH before WALK_tSTIM_ will exceed the benefits of walking practice (WALK), tAIH + WALK_tSHAM_, or Placebo + WALK_tSTIM_ on enhancing the performance of the trained task of overground walking. Justification for the treatment sequence of tAIH followed by WALK_tSTIM_ is based on the estimated time (minutes) required for tAIH to facilitate expression of BDNF.^27^ Applying tAIH ∼1 h before WALK_tSTIM_ may promote temporal alignment of mechanisms of WALK_tSTIM_ neuromodulation with complementary mechanisms of tAIH-induced plasticity that involve BDNF. Details on these interventions are below.

#### Walking practice

Participants receive eight 45-min WALK sessions over 2 consecutive weeks. The WALK sessions consist of intensive walking-related functional tasks using a skill-based training approach.^6^ The training includes activities related to walking speed (10MWT), initiation and balance (TUG), and walking endurance (6MWT). Recent studies found that skill-based walking practice is more consistent with community walking, providing meaningful gains in walking function after neurological injury.^28–31^ Walking practice emphasizes learning sensorimotor skills for community walking, including walking speed, endurance, stepping balance, and initiation.^30^ Participants may rest up to 15 min during the practice sessions. During the WALK sessions, the physical therapist trainer will provide physical assistance as needed for safety. Step count, peripheral blood oxygen saturation (SpO_2_), heart rate (HR), and blood pressure (BP) are measured at each session.

#### Therapeutic acute intermittent hypoxia (tAIH/Placebo)

Each participant receives eight ∼40-min tAIH sessions (2 weeks, four sessions per week) of tAIH or sham. A tAIH session consists of 15 episodes of 90-sec breathing low oxygen (F_I_O_2_ = 0.10 ± 0.02, i.e., 10% O_2_) or breathing room air (F_I_O_2_ = 0.21 ± 0.02, i.e., 21% O_2_) for sham with 60-sec intervals of room air (Fig. 4). We provide the treatments by a custom automated air delivery system as previously described.^32^ In brief, the delivery system alternately directs an air from a pressure-swing adsorption low-oxygen generator (HYP-123; Hypoxico Inc., New York, NY) and a flow-matched blower source to the non-rebreather face mask. We monitor and record SpO_2_ and HR at 1-sec intervals and BP every fifth breathing interval using a vital monitor (Masimo Root, Radical-7; Masimo Corp., Irvine, CA).

**FIG. 4. f4:**
[figure not shown]
Illustration of intervention protocols (**A**) A participant receives a tAIH sequence consisting of fifteen 1.5-min episodes of breathing low oxygen (10% O_2_) with 1-min intervals of breathing room air (21% O_2_). (**B**) We monitor the participant's heart rate (HR), blood oxygen saturation (SpO_2_), and blood pressure (BP) during tAIH intervention. (**C**) During the tSTIM protocol, participants receive a sequence of 1-ms bursts of electrical stimulation at 30 Hz with a 10-kHz carrier frequency that targets the thoracolumbar region (T_11_–L_2_). We set the stimulation amplitude to a subthreshold intensity between 0 and 200 mA before the intervention session (**D**). The subthreshold stimulation is active during 45 min of skill-based walking practice (WALK_tSTIM_). tAIH, therapeutic intermittent hypoxia; tSTIM, transcutaneous spinal stimulation; WALK_tSTIM_, transcutaneous spinal stimulation-enhanced walking therapy.

#### Spinal stimulation during walking practice (WALK_tSTIM_/WALK_tSHAM_)

Participants receive eight 45-min sessions (2 weeks, four sessions per week) of either the combination of WALK and transcutaneous electrical stimulation (WALK_tSTIM_) or WALK and transcutaneous sham stimulation (WALK_tSHAM_). A research team member, not blinded to the intervention, configures the portable stimulation system (SCONE; SpineX Inc; Los Angeles, CA; Fig. 4C,D) and places the device superficial to the thoracolumbar region of the spinal cord. The stimulating electrodes are placed at the midline on the trunk superficial to the spinous processes of the T_11_–T_12,_ and L_1_–L_2_ vertebrae.^33,34^ The grounding electrodes are placed over the left and right iliac crests. The device can deliver mono- and biphasic current with a 1-ms pulse width at a 30-Hz base frequency and a 10-kHz carrier frequency. However, a biphasic waveform is preferred for delivering high-amplitude stimulation with minimal discomfort.^17,35^ This is likely attributable, in part, to the biphasic waveform's capacity to attenuate unmyelinated c-fibers activity and to penetrate deeper because of lower tissue impedance.^36^ During the WALK_tSTIM_ conditions, the current is set to 80% of the motor threshold, as detailed previously,^33^ and 0 mA during the WALK_tSHAM_ condition. The motor threshold corresponds to the minimum stimulation intensity to achieve an involuntary motor activity in the lower extremities.

